#### Trial period: weeks 0–8

The research nurses will send weekly emails for 8 weeks, encouraging the participants’ adherence to the application and asking them to record their responses on the e-PRO system. The research team can evaluate a patient’s progress using the application (e.g., the number of times and duration of use for each application) on the server.

#### Follow-up period: weeks 8–24

At week 24, the participants will receive an email encouraging them to provide their responses on the e-PRO system.

#### Termination assessment

If participants withdraw consent for assessment, they will not be followed up. Subjects will be excluded from the intention-to-treat (ITT) cohort of the trial if their characteristics are found to meet any exclusion criteria at baseline (e.g., aged under 20 years) after participation.

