#### Eligibility criteria for participants

Each participant must satisfy all of the following inclusion criteria and none of the exclusion criteria.

Inclusion criteria are as follows:1. Patients with a cancer diagnosis and awareness of the same diagnosis2. Patients aged 20 years or older3. Smartphone users who are capable of using an electronic patient-reported outcome (e-PRO) system with a smartphone4. Patients with an estimated prognosis of more than 6 months5. Patients who expect to concentrate on the intervention for about two months after participation in this study (e.g., those who do not plan to use cell-damaging anticancer drugs with strong side effects).

Exclusion criteria are as follows:1. Patients who do not understand Japanese2. Patients with psychiatric symptoms (e.g., dementia, cognitive impairment, and severe depression with suicide ideation) who have been identified by attending physicians as inappropriate for the study3. Individuals who have received face-to-face CBT4. Persons who received smartphone CBT or participated in our previous study, the “SMILE PROJECT.”

Eligibility criteria for study personnel are as follows:

Encouragement emails will be handled by personnel who are qualified in health care, such as nurses.

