#### Termination rules for participants

Discontinuation of protocol treatment

If a participant meets any of the following conditions, the research team can discontinue their access to the application. However, the participant will not be considered to have dropped out of the trial at that stage and will receive the protocol assessments if (1) the participant intends to stop the protocol treatment; (2) the research team judges that the risk of the protocol treatment is greater than the benefit for any reason; (3) the research team evaluates that it is difficult to continue the protocol treatment owing to clinical deterioration; and (4) the research team assesses that it is inappropriate to continue the protocol treatment for any reason (e.g., when identity theft, duplicate entry, etc., are detected).

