## Blinding

Neither the participants nor the study personnel will be blinded to the intervention that each participant is receiving through the conduct of the trial. The assessment of all the primary and secondary outcomes will be self-reported by the participants and therefore not blinded. The statisticians will be blinded to the allocation through the statistical analyses by analyzing the datasets prepared by the study personnel in which all components are denoted only by a letter.

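### The ITT cohort may drop randomised participants later found to have met any exclusion criterion, including a physician-judged psychiatric one, with no blinded decision

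*Protocol article*

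**What the plan says.** Termination assessment sets the rule: "Subjects will be excluded from the intention-to-treat (ITT) cohort of the trial if their characteristics are found to meet any exclusion criteria at baseline". The bracketed example and the timing follow: "e.g., aged under 20 years) after participation". This is the only place in the article's text that describes the ITT cohort; Primary analyses gives the model but names no analysis population.

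Under Eligibility criteria for participants, the second exclusion criterion covers patients with psychiatric symptoms "who have been identified by attending physicians as inappropriate for the study". Its examples include severe depression with suicidal ideation. The age limit stands in the other list, among the inclusion criteria: "Patients aged 20 years" or older.

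Blinding states: "Neither the participants nor the study personnel will be blinded to the intervention that each participant is receiving". The statisticians are to be blinded by "analyzing the datasets prepared by the study personnel in which all components are denoted only by a letter".

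Eligibility is checked by telephone by central coordinators. Randomisation follows e-consent, the baseline assessment and completion of the psychoeducation component (Electronic informed consent and randomization at week 0).

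**The concern.** An intention-to-treat set protects the comparison because membership is settled at randomisation and nothing learned afterwards can change it. This rule reopens membership after entry, on every exclusion criterion, and states no safeguard on who decides or what they may know.

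For an objective fact such as age this hardly matters. The psychiatric criterion is different. Whether a patient's symptoms made them unsuitable at entry is a judgement, and it concerns nearly the same construct as the primary outcome. If that judgement is made late, it can be influenced by how the patient has fared and by which components they received. Coding components by letter does not help, because it acts only after the dataset has been assembled.

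At stake are the three main-effect contrasts (BA, AT, PS), each tested at an unadjusted two-sided 0.05 and used to decide what enters the optimised package. Readers would also take the ITT label as an assurance that no such selection had occurred.

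**Working it through.** **1. The plan's own figure.** Inputs from Sample size estimation and Primary analyses: SMD 0.3 (SD = 1), two-sided alpha 0.05, power 0.80.

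n per level = 2 × (1.960 + 0.842)² / 0.3² = 174.4, rounded up to 175, so 350 in total. This reproduces the stated 350. The final target of 16 × 22 = 352 gives 176 against 176 for each main effect, SE = √(2/176) = 0.1066 SD, and power 80.4% before dropout. The point challenges none of these figures.

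**2. Power is not the issue.** Balanced removal of 1%, 2%, 5% or 10% of the 352 leaves power at 80.0%, 79.6%, 78.3% or 76.1%.

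**3. Bias, removal at one level only.** The article gives no removal rates, so f and k are assumptions. Let a fraction f be removed from one level of a component, with week 8 scores k SD worse than that level's average.

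- Shift of the contrast: b = f × k / (1 − f)
- SE = √(1/176 + 1/(176(1 − f)))
- Type I error = Φ(−1.96 + b/SE) + Φ(−1.96 − b/SE)

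| f (of 176) | k | b (SD) | Share of 0.3 | Type I error |
|---|---|---|---|---|
| 1% (about 2) | 1 to 2 | 0.010 to 0.020 | 3 to 7% | 5.1 to 5.4% |
| 2% (about 4) | 1 to 2 | 0.020 to 0.041 | 7 to 14% | 5.4 to 6.7% |
| 5% (about 9) | 1 to 2 | 0.053 to 0.105 | 18 to 35% | 7.8 to 16.4% |

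**4. Bias, removal at both levels but unequal.** Let k be the distance from those who remain, equal at both levels. The shift is then (difference in removal fractions) × k. For a 3-point difference (about 5 of 176):

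- k = 1: b = 0.030 SD (10% of 0.3), b/SE = 0.281, type I error 5.9%.
- k = 1.5: b = 0.045 SD (15% of 0.3), b/SE = 0.422, type I error 7.1%.

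The type I formula is symmetric in b, so the same figures hold whichever level loses more patients.

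**5. What these figures leave out.** They use unadjusted week 8 scores. The planned model includes baseline PHQ-9, and allocation is stratified on it, so part of the outcome distance of patients who were already more depressed at entry would be absorbed.

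**6. Scope of the rule.** The operative words concern exclusion criteria. The example, age under 20, fails an inclusion criterion and is not on the exclusion list. Read by its wording, the rule misses its own example. Read by its example, it reaches failed inclusion criteria that it does not mention.

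**The case against.** The strongest defence is that the rule is tied to status at baseline. A patient who deteriorates after randomisation does not thereby become ineligible at entry. The psychiatric criterion, naturally read, asks whether a physician had already identified the patient as unsuitable. Oncologists hand out the invitation card and coordinators screen by telephone, so most such cases should be caught before randomisation. The phrase about timing could also cover findings during the psychoeducation run-in, before allocation. The age example suggests that the authors had simple eligibility errors in mind.

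This stands to the extent that bias is possible rather than built in. It does not remove the defect: the text says any exclusion criterion, sets no time limit, and does not confine the rule to the run-in. An ITT cohort consists of randomised people, so the rule as written removes randomised people.

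A reader might infer more than the article supports:

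- **That the bias favours the components**, because participants with more lessons are more likely to be found ineligible. Everyone receives weekly emails for eight weeks, the assessment schedule is described without differences by combination, and nothing says that worksheets are reviewed for eligibility. Neither the mechanism nor the direction is in the text.
- **That staff who know the allocation make the decision.** No decision-maker is named. The text establishes only that study personnel are unblinded, that they prepare the datasets, and that no blinded decision is specified.
- **That a duplicate entrant would be counted twice.** Termination rules for participants allows access to be stopped ("e.g., when identity theft, duplicate entry, etc., are detected") while assessments continue. That governs app access and follow-up, not the analysis set, so double counting is not established.

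**Conclusion.** The point holds as a badly fixed rule. The set called ITT is not intention-to-treat, because randomised participants can leave it on grounds that include a physician's judgement related to the primary outcome, in an open trial and without a stated blinded decision. It would be too strong to say that the randomised comparison is broken: removal on objective baseline facts, decided blind to allocation, would cause no expected bias. Judged or allocation-aware removals can bias a component contrast in either direction.

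The size is unknown, because the article gives no expected rate of late ineligibility. On the assumed inputs above, the effect is negligible at 1% removed from one level and becomes material at differentials of a few percent. Telephone screening before randomisation and adjustment for baseline PHQ-9 both argue for the lower end. The mismatch between the rule and its example is a separate drafting fault that leaves the scope unclear.

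**What to change.** - Define the primary analysis set as all randomised participants, analysed as allocated.
- Permit removal only for objective facts fixed before randomisation, such as age or participation in the earlier study, adjudicated by someone blind to allocation and outcome.
- Make the example match the rule, either by citing a true exclusion criterion or by stating that the rule also covers failed inclusion criteria.
- Report the analysis without other ineligible participants as a separately named sensitivity analysis.

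The cost is about two sentences and one additional model run. The planned 352 and its power are unchanged. The downside is that a few ineligible participants stay in the primary set.

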#### Assignment of interventions

Randomization and allocation concealment

The allocation will be stratified by the baseline PHQ-9 score (9 or less vs. 10 or more). We will use permuted block randomization to ensure balance in the number of subjects allocated to each combination because in the fully factorial design, imbalance in the allocated numbers among the factors would reduce the statistical power of the study. An independent data center will generate computer-generated random allocation sequences, which are maintained centrally, and the results of the assignment will determine which components are presented to the participants on their smartphone.

## Blinding

Neither the participants nor the study personnel will be blinded to the intervention that each participant is receiving through the conduct of the trial. The assessment of all the primary and secondary outcomes will be self-reported by the participants and therefore not blinded. The statisticians will be blinded to the allocation through the statistical analyses by analyzing the datasets prepared by the study personnel in which all components are denoted only by a letter.

### Plans to promote participant retention and complete follow-up

The outcome data will be collected even when a participant has not completed the allocated intervention unless he or she has expressed a wish to completely withdraw from the study. When a participant fails to fill in the scheduled assessments, reminders will be sent in 24 h and 48 h via an automated popup on the smartphone. If participants fail to provide their responses regarding the PHQ-9, a research nurse blinded to the assignment will send an e-mail to the subjects to elicit their answers. The participants will receive modest compensation for the time it requires to complete the questionnaire: 2000 yen when they complete the week 0 assessment, 1000 yen when they complete the week 4 assessment, 1000 yen when they complete the week 8 assessment, and 1000 yen for completing the week 24 assessment.

#### Data management

A secure, web-based, password-protected database will be used to manage recruitment, eligibility assessments, randomization, scheduling and tracking, baseline and follow-up assessments, and the delivery of the allocated interventions. All the assessment data will be checked automatically for integrity by this platform. The security of the data transfer between the application and the server will be guaranteed through the Secure Socket Layer (SSL).

### Statistical analysis and power calculation

#### Primary analyses

We will use the mixed-effects repeated-measures (MMRM) analysis [41] to estimate the mean difference in change scores on the PHQ-9 for each component. We will use the following regression model for the outcome variable of *i*th participant and *j*th visit ($$i=\mathrm{1,2},\dots ,n;j=\mathrm{1,2},\dots ,T$$),$$E\left[{Y}_{ij}\right]={\beta }_{0}+{\beta }_{1}\times B{A}_{i}+{\beta }_{2}\times {AT}_{i}+{\beta }_{3}\times {PS}_{i}+{\beta }_{4}\times visi{t}_{j}+{\beta }_{5}\times ag{e}_{i}+{\beta }_{6}\times se{x}_{i}+{\beta }_{7}\times baseline PHQ{9}_{i}+{\beta }_{8}\times {BA}_{i}\times visi{t}_{j}+{\beta }_{9}\times {AT}_{i}\times visi{t}_{j}+{\beta }_{10}\times {PS}_{i}\times visi{t}_{j}$$where $${Y}_{ij}$$ is the outcome variable, $$B{A}_{i}, {AT}_{i}$$ and $${PS}_{i}$$ are treatment indicators of the three components, and $$visi{t}_{j}$$ is a nominal variable indicating the visit time. For the within-participant covariance matrix model, we will adopt the unstructured structure. We calculated pre–post effect sizes by dividing the estimated mean changes from baseline to week 8 by the observed SD of baseline scores, and between-group effect sizes (SMD) at week 8 by dividing the estimated mean differences in change scores between groups by the observed SD of week 8 scores. No adjustment for multiple testing will be applied in the estimation of the statistical significance of the main and interaction effects in this model, and the conventional threshold for statistical significance (*p* < 0.05, two-sided) will be used because of the following: in the optimization phase of the MOST framework [42], the emphasis is on making a decision about what components will make up the optimized intervention, and factorial designs usually evaluate multiple, completely different interventions that could have been assessed in separate trials and, conventionally, the multiple hypotheses have been tested independently for these trial designs [43, 44].

#### Secondary analysis

The secondary analysis will use the same models as those used in the primary analysis. MMRM analysis will be used to estimate the mean differences in changed scores on the GAD-7 questionnaire for each component. So, we will perform the MMRM analyses involving second-order interaction effects of the three components as secondary analyses.

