### Secondary outcome measure

The secondary outcome is the self-administered Generalized Anxiety Disorder-7 (GAD-7) [23] score at week 8.

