## Sample size estimation

In the smartphone psychotherapy intervention used in this study, CBT, including behavioral activation and cognitive restructuring, showed a statistically significant effect among 164 depressive patients, with an effect size of 0.3–0.4. In this study, to determine an effect size of 0.3, for each intervention factor (problem-solving skills, behavioral activation, assertive communication) and its interaction at an alpha = 0.05 and a beta = 0.20, we need a total sample size of 350. We estimated the effect size as 0.3 because problem-solving skills or behavioral activation had the same effect as full-package CBT in a recent comprehensive meta-analysis [45]. To achieve this, the sample size needs to be 22 for each of the 16 combinations, and the total sample size is therefore 16 × 22 =352.

Although we expect a dropout of approximately 20%, we will use mixed-effects repeated measures analysis.

As a study with more than five measurement points is known to require 30–50% fewer participants for the same power compared to a pre-to-post-only assessment, we set the final target sample size of our study conservatively, as estimated above.

If the case accumulation is smoother than expected, we will continue the case accumulation aiming at a sample of 787, which will enable an effect size of 0.2.

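### The GAD-7 model carries over baseline PHQ-9 as its only severity covariate; adding the collected baseline GAD-7 would gain precision at almost no cost

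*Protocol article*

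**What the plan says.** The Primary analyses section introduces an MMRM "to estimate the mean difference in change scores on the PHQ-9 for each component" and writes out a single regression equation. The outcome symbol in it is generic. The covariates are named: age, sex and baseline PHQ-9, the last appearing in the equation as "baseline PHQ{9}_{i". There is no term for baseline GAD-7.

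The Secondary analysis section then says: "The secondary analysis will use the same models as those used in the primary analysis". It continues: "MMRM analysis will be used to estimate the mean differences in changed scores on the GAD-7 questionnaire for each component". It does not say whether baseline GAD-7 replaces baseline PHQ-9, joins it or stays out.

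Other sections bear on this:
- Secondary outcome measure: "The secondary outcome is the self-administered Generalized Anxiety Disorder-7 (GAD-7) [23] score at week 8". No other secondary outcome is listed.
- Background characteristics: GAD-7 is measured at baseline, next to PHQ-9, under clinical characteristics.
- Assignment of interventions: "The allocation will be stratified by the baseline PHQ-9 score (9 or less vs. 10 or more". Baseline GAD-7 plays no part in the allocation.

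**The concern.** The baseline value of an outcome is usually among its best predictors. Here the equation names the baseline of a different scale, and the text transfers that equation to GAD-7 unchanged. An analyst who follows it would model change in anxiety adjusted for baseline depression and not for baseline anxiety.

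Subtracting baseline GAD-7 is not the same as adjusting for it. Subtraction fixes its coefficient at 1, whereas a covariate lets the data estimate it. When the true coefficient is below 1, regression to the mean stays in the residual. A chance difference between component levels in baseline GAD-7, beyond what PHQ-9 explains, then passes partly into the effect estimate.

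At stake are the width of the confidence intervals for the three component effects on anxiety, which the stated aim names together with depression, and their sensitivity to chance imbalance. The PHQ-9 primary analysis is not affected.

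**Working it through.** **The plan's own figure.** The article states, for an effect size of 0.3, "at an alpha = 0.05 and a beta = 0.20, we need a total sample size of 350", with the threshold given as "p* < 0.05, two-sided". The normal formula per level of a component is n = 2(1.960 + 0.842)²/0.3² = 174.4, rounded up to 175, so 350 in total. This reproduces. The target of 352 gives 176 against 176 per component, with power 0.80. It is an unadjusted calculation and the article makes no precision or power claim for GAD-7, so it supplies only the scale for what follows.

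**Inputs for the check.** The article gives no correlations. The following are assumptions, with equal SDs (set to 1) at both times and a single post-baseline visit:
- a = baseline to week-8 GAD-7: 0.5-0.7, central 0.6
- b = baseline PHQ-9 to week-8 GAD-7: 0.40-0.55, central 0.45
- c = baseline PHQ-9 to baseline GAD-7: 0.70-0.75, central 0.7

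**Formulas for the residual variance.**
- GAD-7 change adjusted for baseline PHQ-9 only (literal reading): V₁ = 2 − 2a − (b − c)²
- Both baselines as covariates (proposed): V₂ = 1 − (a² + b² − 2abc)/(1 − c²)

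With baseline GAD-7 in the model, change scores and raw scores give the same component effects, so V₂ serves for both.

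**Central case.**
- V₁ = 2 − 1.2 − (0.45 − 0.7)² = 0.8 − 0.0625 = 0.7375
- V₂ = 1 − (0.36 + 0.2025 − 0.378)/0.51 = 1 − 0.3618 = 0.6382
- Reduction: 1 − 0.6382/0.7375 = 0.135, about 13%
- Standard error ratio without the covariate: √(0.7375/0.6382) = 1.075, about 7% larger

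**Ends of the assumed range.**

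| a, b, c | V₁ | V₂ | Reduction |
|---|---|---|---|
| 0.7, 0.40, 0.75 | 0.4775 | 0.4743 | 0.7% |
| 0.6, 0.45, 0.70 | 0.7375 | 0.6382 | 13% |
| 0.5, 0.55, 0.70 | 0.9775 | 0.6716 | 31% |

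The gain is positive over the whole grid of assumed values, from about 1% to about 31%.

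**Replacing instead of adding.** If baseline GAD-7 took the place of baseline PHQ-9, the residual variance would be 1 − a². In the first row that is 0.51 against 0.4775, a loss of 7%. In the last row it is 0.75 against 0.9775, a gain of 23%. Replacement alone is therefore not sure to help.

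**Chance imbalance, central case.** Given PHQ-9, the standard error of the baseline GAD-7 difference at 176 against 176 is √(0.51 × 2/176) = 0.076 SD. With both covariates the coefficient of baseline GAD-7 is (0.6 − 0.45 × 0.7)/0.51 = 0.559. The change score forces it to 1, an error of 0.441. A one-standard-error imbalance then shifts the component effect by 0.441 × 0.076 = 0.03 SD. A two-standard-error imbalance shifts it by 0.07 SD, or 22% of the planning effect (0.067/0.3).

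**Power for 0.3 SD, central case.** Without dropout it is 0.91 under the literal reading and 0.94 with both baselines. If the expected 20% dropout is treated as simply lost (about 141 per level), it is 0.83 and 0.88.

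**The case against.** The strongest reply is that the equation stands under the PHQ-9 analysis, so its baseline PHQ-9 term may simply be that outcome's own baseline. The same models could then mean the same form with each outcome's own baseline, a detail that the full protocol or analysis plan may settle. That reading is possible and cannot be excluded. It does not remove the point. The article chose to write out the covariates and to state that they carry over, and an analysis with baseline GAD-7 would depart from its literal words. Both readings call for the same sentence.

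Three stronger readings are tempting, and the article supports none of them:
- A reader might infer that GAD-7 is analysed without its own baseline. The target is a difference in GAD-7 change scores, so the baseline does enter, by subtraction. Only the covariate is missing.
- A reader might infer that the component effects are biased. Randomisation keeps them unbiased on average. Baseline PHQ-9, which is stratified on and adjusted for, also takes up part of any anxiety imbalance. What remains is the modest conditional shift shown above.
- A reader might infer that a large loss is certain. No correlation is given, the gain can be as small as about 1%, and in the central case power for 0.3 SD stays above 0.80 even with dropout.

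**Conclusion.** The point holds as a minor one. As written, the GAD-7 analysis leaves out a baseline covariate that is already collected, which costs precision but not validity. Adding it would cut the residual variance by about 1-31%, and by about 13% in the central case, equivalent to roughly 0.135 × 352 = 47 participants.

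These figures rest wholly on assumed correlations, equal SDs at both times and a single-visit simplification of the MMRM. Only the direction is secure: adding a covariate to the model cannot raise the population residual variance. The article's sample size and its primary analysis are untouched.

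**What to change.** In the Secondary analysis section, state that the GAD-7 model is the primary model with baseline GAD-7 added as a covariate, and that baseline PHQ-9 is kept because randomisation is stratified on it. Adding is preferable to replacing: it respects the stratification, and replacement alone can lose precision. A baseline-by-visit interaction is optional; the primary model has none.

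The cost is one sentence and one degree of freedom. No new data are needed. If the full protocol or analysis plan already specifies this, only the article's wording needs to be brought into line, before the data are analysed.
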